### Wearable sensor

As a wearable sensor, the “Healthdot” (Philips Electronics Nederland B.V.) is used [20]. This is a wearable patch of five to three centimeters that weighs 13.6 g. The device is attached to the left lower rib of the patient on the mid-clavicular line. The accelerometer-based device uses seismocardiography and displacement along different axes to calculate HR, RR, posture, and activity levels every 5 min [21, 22]. It then transmits these data directly to a cloud via a low-power wide-area network (LoRaWAN), from where it can be transferred to the hospital IT infrastructure. The real-time data of measurements are displayed in tabular and graphical form on a dashboard called IntelliVue Guardian Software (version E.01.00) and are available for healthcare professionals on their computer desktop after logging in.

The conventional EWS used in the AAW uses RR, HR, oxygen saturation, oxygen supply, systolic blood pressure, consciousness, and temperature with predetermined thresholds to calculate a EWS between 0 and 20. The data from the wearable sensor are used to automatically calculate a sensor EWS solely based on HR and RR, which uses the same thresholds as the conventional EWS, resulting in a sensor EWS between 0 and 6. This score is converted to a risk band, which can be green (EWS ≤ 1), orange (EWS 2), or red (EWS >2), indicating the risk of deterioration. In case the risk band remains increased for three subsequent periods of 15 min, a notification is displayed on the dashboard. This notification can be visualized by nurses and physicians in the AAW when logged into the dashboard. The nurses and physicians of the AAW are free to act upon these notifications, for instance by performing an additional check-up. When a patient remains within the same risk band or improves within 45 min, no notification is displayed.

The wearable sensor is employed for the full extent of time specified by the manufacturer, which is 14 days. It is possible that a patient in the sensor group wears the wearable sensor for less than 14 days. Possible reasons are accidental detachment; removal due to unexpected side effects, such as skin rash; removal by a healthcare provider for other reasons; or removal due to patient withdrawal. In these cases, there is no replacement for the wearable sensor. Reattaching the wearable sensor is not possible because the adhesive layer is designed for single use only. If a wearable sensor is detached while the patient is admitted to the AAW, a new wearable sensor is attached if permitted by the patient. In line with the instructions for use, detachment is only necessary when a patient needs an MRI scan. To prevent unnecessary detachment of the wearable sensor after hospital discharge, patients receive an information card with instructions for healthcare providers in case the healthcare provider is in doubt as to whether a medical interference requires the removal of the sensor.

### Data collection and management

Data are collected from four different sources. Firstly, data on medical treatment, laboratory tests, patient characteristics, and primary and secondary outcomes, such as whether a patient was safely discharged, are retrieved from the Electronic Medical Record (EMR). Secondly, for the sensor group, wearable sensor data of the overall period up to 14 days are collected. Thirdly, supplementary data pertaining to the primary outcome, specifically healthcare usage after discharge (e.g., readmissions in other hospitals), will be obtained from patient questionnaires. The questionnaires also include information regarding the patient’s experience with the wearable sensor to assess feasibility. Since there is currently no validated questionnaire aligned with our study objectives, self-constructed questionnaires will be employed. Fourthly, data from questionnaires and interviews with healthcare professionals are collected at the end of the trial. Healthcare professionals will be selected using a stratified sampling method, ensuring a representative distribution of all specialties that operate in the AAW. These data will be used to investigate facilitators and barriers for implementing continuous monitoring in usual care in the AAW.

All collected data are protected according to data protection standards of the Netherlands and the European Union. All EMR and wearable sensor data are stored in pseudonymized form on secured hospital databases and are only accessible by authorized persons for this project. The questionnaire data are stored in pseudonymized form using the Research Manager platform (version 5.57.0). On signing the consent form, participants agree to the utilization of their data collected until the moment of potential withdrawal. Also, they agree to share relevant data with the involved researchers from the university or from regulatory authorities. Furthermore, patients are requested to provide consent for the utilization of their data in future studies pertaining to remote healthcare. No collection of biological specimens for storage will be conducted.

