**Methods:**

A total of 800 patients admitted to the AAW, for whom it is equivocal whether they can be discharged directly after their AAW stay, will be randomized to either receive usual care without (control group) or with additional continuous monitoring of heart rate, respiratory rate, posture, and activity, using a wearable sensor (sensor group). Continuous monitoring data are provided to healthcare professionals and used in the discharge decision. The wearable sensor keeps collecting data for 14 days. After 14 days, all patients fill in a questionnaire to assess healthcare use after discharge and, if applicable, their experience with the wearable sensor. The primary outcome is the difference in the percentage of patients who are safely discharged home directly from the AAW between the control and sensor group. Secondary outcomes include hospital LOS, AAW LOS, intensive care unit (ICU) admissions, Rapid Response Team calls, and unplanned readmissions within 30 days. Furthermore, facilitators and barriers for implementing continuous monitoring in the AAW and at home will be investigated.

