### Outcomes

The primary outcome is the difference between the control and sensor group in the percentage of patients who are safely discharged from the hospital directly after AAW stay. A safe discharge is defined as a discharge without following unplanned hospital readmission, ED revisit, or mortality within 30 days. Secondary outcomes are LOS in the AAW, LOS in the in-hospital wards, percentage of RRT calls during AAW and hospital stay, percentage of ICU admissions during AAW and hospital stay, and percentage of unplanned readmissions to the hospital within 30 days after hospital discharge. Furthermore, facilitators and barriers for implementing continuous monitoring in usual care in the AAW will be assessed by questionnaires and interviews with healthcare professionals. Also, for the sensor group, the feasibility of remote home monitoring with the wearable sensor is assessed, including the duration for which the sensor was worn, factors leading to its early detachment, user complaints regarding wearing the sensor, and restrictions in daily activities.

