**Fig. 1 Fig1:**
[figure not shown]
An outline of the trial pathway

Patients in the sensor group receive a wearable sensor for continuous monitoring of HR, RR, posture, and activity by a nurse, in addition to usual care, immediately after allocation in the AAW. The data from the wearable sensor is accessible for nurses and physicians in the AAW on a computer dashboard (see Fig. 2). No alarms will be generated to avoid potential alarm fatigue. Instead, notifications of deteriorating patients are displayed on the dashboard (see the “Wearable sensor” section). During the daily bedside rounds, physicians are asked to consider the continuous monitoring data, in addition to the data usually available, in deciding whether a patient can be discharged. As there is no gold standard on how to interpret these continuous monitoring data with regard to patient discharge in such a heterogeneous population, physicians are not provided with specific instructions on how to appraise these data. However, vital signs have been demonstrated to predict patient deterioration and we therefore hypothesize that the availability of these continuous vital sign measurements will help clinical decision-making with regard to patient discharge. There are no restrictions regarding concomitant care during the trial.

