**Fig. 2 Fig2:**
[figure not shown]
Upper graph: Sensor Early Warning Score based on heart rate (HR) and respiratory rate (RR). Center and lower graphs: HR (green) and RR (orange) of a patient, respectively

After admission to the AAW, patients are either discharged home, to a nursing home, or admitted to an in-hospital ward. In all cases, for patients in the sensor group, the wearable sensor remains attached for a total of 14 days. However, after AAW stay, these measurements are no longer presented to healthcare professionals, but only analyzed retrospectively. After 14 days, the wearable sensor is removed by the patient and patients of both the control and sensor group are asked to fill in the patient questionnaire. Patient follow-up will be completed 30 days after hospital discharge.

A schedule of enrolment, interventions, and assessments of this trial is shown in SPIRIT format in Table 2 [18]. Hospital readmissions, ED revisits, and mortality are monitored until 30 days after hospital discharge. At the end of the trial, healthcare professionals are asked to fill in a questionnaire to assess satisfaction and the usability of the wearable sensor. Facilitators and barriers for implementing continuous monitoring in usual care in the AAW and at home will be assessed by patient questionnaires, healthcare professional questionnaires, and interviews with healthcare professionals.

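### The questionnaire that supplies events at other hospitals is placed at day 14, so about 18 of the 30 days in the primary outcome have no stated source for them

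*Protocol article*

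**What the plan says.** The Outcomes section sets the window: "A safe discharge is defined as a discharge without following unplanned hospital readmission, ED revisit, or mortality within 30 days". The Intervention section repeats it as a follow-up commitment: "Hospital readmissions, ED revisits, and mortality are monitored until 30 days after hospital discharge".

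The Data collection and management section gives two sources for this outcome. Primary and secondary outcomes, "such as whether a patient was safely discharged, are retrieved from the Electronic Medical Record (EMR"), come from the hospital's own system. In addition, "supplementary data pertaining to the primary outcome, specifically healthcare usage after discharge (e.g., readmissions in other hospitals), will be obtained from patient questionnaires".

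The timing of the questionnaire is given twice. Abstract, Methods: "After 14 days, all patients fill in a questionnaire to assess healthcare use after discharge". Intervention section, on this same form: "After 14 days, the wearable sensor is removed by the patient and patients of both the control and sensor group are asked to fill in". Sensor attachment takes place "immediately after allocation in the AAW", and wear lasts 14 days in total, so the clock starts at allocation and not at discharge. A footnote to Table 2 puts discharge typically within 48 h. The body of Table 2 is not shown.

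**The concern.** This is a single-centre trial, and by adding a second source for care elsewhere the protocol accepts that its own record is incomplete. That second source is collected before half of the outcome window has passed. The article states the source, its purpose and its time, and at that time the source cannot serve the purpose. An analysis plan cannot recover events that nobody asked about.

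The error has one direction: a patient with an unseen outside event is scored safe. Only patients discharged directly from the ward can be misclassified in this way, and the intervention aims to increase their number. If earlier discharge did some harm, part of that harm would be hidden, and more of it in the arm that discharges more.

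**Working it through.** **1. Coverage.** Days covered after discharge = 14 − days from allocation to discharge. Days uncovered = 30 − days covered.

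| Discharge at | Covered | Uncovered |
|---|---|---|
| 24 h | 13 | 17 (57%) |
| 48 h | 12 | 18 (60%) |
| 72 h | 11 | 19 (63%) |

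Even if the 14 days ran from discharge, 30 − 14 = 16 days would be uncovered.

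**2. Direct discharge.** The Sample size section gives 40% (control) and 50% (sensor) *safely* discharged, midpoint 45%. The proportion discharged directly must be larger: safe / (1 − e), where e is the 30-day event risk after direct discharge. With e = 10%, 0.45 / 0.90 = 50%. With e = 20%, 0.45 / 0.80 = 56%.

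**3. Misclassified share of all randomised patients.** Share = direct discharge × e × u × w, where u is the share of events at other hospitals and w is the share of events after the questionnaire. None of e, u or w is in the document. Set A assumes e 10-20%, u 10-30%, w 35-50%.
- Low: 0.50 × 0.10 × 0.10 × 0.35 = 0.0018 (0.2%)
- High: 0.5625 × 0.20 × 0.30 × 0.50 = 0.0169 (1.7%)

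This takes every late outside event as absent from the hospital's record, so it is an upper reading for each set of inputs.

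**4. Between-arm difference, equal event risk.** A true 10-point difference in safe discharge shifts by 0.10 / (1 − e) × e × u × w. Set B is a second range: e 10-30%, u 5-20%, w 40-60%.
- Set A: (0.10 / 0.90) × 0.10 × 0.10 × 0.35 = 0.04 points, to (0.10 / 0.80) × 0.20 × 0.30 × 0.50 = 0.4 points
- Set B: (0.10 / 0.90) × 0.10 × 0.05 × 0.40 = 0.02 points, to (0.10 / 0.70) × 0.30 × 0.20 × 0.60 = 0.5 points

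The observed difference would be about 10.0-10.5 points.

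**5. Adverse scenario: the sensor adds only unsafe discharges.** Assume direct discharge of 50% (control) and 60% (sensor), with true safe discharge of 40% in both. Unsafe direct discharges are then 10% and 20%, and the false benefit is (0.20 − 0.10) × u × w.
- Set B: 0.10 × 0.05 × 0.40 = 0.2 points, to 0.10 × 0.20 × 0.60 = 1.2 points
- Set A: 0.10 × 0.10 × 0.35 = 0.35 points, to 0.10 × 0.30 × 0.50 = 1.5 points

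The standard error of the difference at 384 per arm is √(2 × 0.40 × 0.60 / 384) = 3.5 points, so even the largest of these is under half a standard error.

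**6. Sample size and power.** The stated total of 768 is reproduced closely: the two-sided unpooled normal formula gives (1.96 + 0.84)² × (0.40 × 0.60 + 0.50 × 0.50) / 0.10² = 384.6 per arm (770 in total), and the pooled version gives 776. Power at 384 per arm is 79.7% for 40% versus 50%. Over Set B with equal event risk it is 79.8-83.2%. The slight rise comes from the overstated difference and is no gain.

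**The case against.** Several points on the other side stand.

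- **The record shown is incomplete.** The Table 2 schedule is where a later contact would appear, and the article condenses a full protocol. The text also says that events are monitored to day 30. A reader might infer that no later ascertainment exists. The documents support only that none is described.
- **The questionnaire is supplementary.** A reader might infer that every outside event after about day 12 is counted as safe. That goes too far: an outside event that reaches the hospital's record, for example by correspondence, would still be scored. The Monitoring and dissemination section also has unanticipated serious adverse events within 30 days entered there, though that covers only some events.
- **Both arms share the gap.** It mainly raises both proportions, while the primary outcome is their difference.
- **Differential response is speculation.** A reader might infer that sensor removal on the same day prompts better response in that arm. No response rates are given, and both arms are asked at the same time. An assumed 20-point response gap under Set A, with 50-65% of events before the questionnaire, would move the difference by 0.50 × 0.10 × 0.10 × 0.50 × 0.20 = 0.05 points to 0.5625 × 0.20 × 0.30 × 0.65 × 0.20 = 0.4 points. A day-30 form would depend on response too.

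None of this supplies a stated source for outside events between about day 12 and day 30. These points limit the size and the certainty of the concern, but the mismatch in timing remains.

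**Conclusion.** The point holds, with moderate severity. As described, the stated source for care at other hospitals cannot cover the stated outcome window: for a 48 h stay about 18 of 30 days are left out. That part is calendar arithmetic on the protocol's own times, and it assumes that the control arm's 14 days also run from allocation.

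The consequence is limited to outside readmissions and ED revisits in that period that do not reach the hospital's record. Its size rests wholly on assumed event rates: about 0.2-1.7% of randomised patients misclassified, a shift in the difference of about 0-0.5 points at equal event risk, and a false sensor benefit of up to about 1.2 points (1.5 under Set A) in the adverse scenario. Against a 10-point target, this alone is unlikely to change the trial's conclusion. The reason to act is the validity of the safety part of the primary endpoint; power and sample size are not at issue.

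**What to change.** Ask the healthcare-use items (readmission, ED visit, which hospital) in both arms at or after day 30 from hospital discharge, which is about day 32 from allocation for a 48 h stay (30 + 2). Leave the sensor-experience items at day 14. Score the primary outcome from the hospital's record plus the later items, report response by arm, and add a sensitivity analysis on the hospital's record alone, so that the arms are also compared on one source that does not depend on response. If the full protocol already has a source for days 12 to 30, stating it would close the point.

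The cost is one short added or moved form on the existing questionnaire platform, a minor amendment and some day-30 non-response. For patients already past day 30, the record-only analysis and the response rates by arm can still be reported.

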### Monitoring and dissemination

Given the previous experience with the wearable sensor [13, 14, 23], no serious adverse events or serious adverse device effects are to be expected. However, if an unanticipated serious adverse event or serious adverse device effect occurs within 30 days, the primary investigator will be notified swiftly and the incident will be documented in the patient’s EMR. In case of a safety-relevant event, the primary investigator will inform the sponsor and ethics committee of the incident within 24 h.

This clinical trial will be audited by an independent auditor to ensure the trial’s integrity. The first visit by the auditor occurs before the start of the trial. Hereafter, visits take place after the first three inclusions and every year until the trial is finished. After finishing the trial, there will be a concluding visit. During these visits, the integrity of the trial process will be assessed, and an evaluation will be conducted to ensure that the involved parties have adequately fulfilled their tasks and responsibilities. Given the perceived low-risk nature of utilizing a commercially available CE certified wearable sensor, the involvement of a data monitoring committee was deemed unnecessary. The trial steering committee, comprising representing physicians (ED, internal medicine, and anesthesiology) and researchers of different fields, will convene in monthly meetings to assess the conduct of the trial. Furthermore, daily support will be provided by two researchers, four charge nurses working in the AAW, and two ED physicians. Amendments to the protocol will be communicated with the ethical committee in accordance with the standards of the Central Committee on Research Involving Human Subjects in the Netherlands. The results will be communicated via multiple scientific publications and conference talks.

### Substudy

As a substudy of this trial, algorithms to predict whether a patient can be discharged safely from the AAW or whether a patient will deteriorate in the AAW will be developed. These predictive algorithms will consider a range of hospital data, including demographics, vital signs, laboratory results, assessments (including EWS), medication use, care activities, and logistical information. Depending on the quality and characteristics of the data, which remain unknown until the trial is conducted, various artificial intelligence techniques, such as logistic regression and Random Forest, may be employed. Hospital data from both the sensor group and control group will be used to develop the algorithms. Furthermore, for the sensor group, additional algorithms will be developed that also utilize wearable sensor data to evaluate the additional value of the sensor. Additionally, for the sensor group, predictive algorithms for patient deterioration after hospital discharge will be developed, considering wearable sensor data and patient demographics. For these reasons, the wearable sensor will not be removed after AAW discharge, but will remain attached for the full extent of time specified by the manufacturer, which is 14 days. Predictive performances of the algorithms will be assessed by the area under the receiver operator characteristic curve, sensitivity, and specificity, among others.

## Intervention

To assess whether adding continuous monitoring to usual care has an effect on patient discharge, this randomized controlled trial includes a control group of patients receiving usual care alone (see Fig. 1). Usual care includes intermittent vital sign monitoring and the calculation of an EWS. This intermittent vital sign monitoring is done manually by nurses every 4 to 8 h, or more if clinically deemed necessary. Thus, patients in the control group will not receive a wearable sensor and will not be continuously monitored. For these patients, the physician only uses the information usually available to decide whether a patient can be discharged.

**Fig. 1 Fig1:**
[figure not shown]
An outline of the trial pathway

Patients in the sensor group receive a wearable sensor for continuous monitoring of HR, RR, posture, and activity by a nurse, in addition to usual care, immediately after allocation in the AAW. The data from the wearable sensor is accessible for nurses and physicians in the AAW on a computer dashboard (see Fig. 2). No alarms will be generated to avoid potential alarm fatigue. Instead, notifications of deteriorating patients are displayed on the dashboard (see the “Wearable sensor” section). During the daily bedside rounds, physicians are asked to consider the continuous monitoring data, in addition to the data usually available, in deciding whether a patient can be discharged. As there is no gold standard on how to interpret these continuous monitoring data with regard to patient discharge in such a heterogeneous population, physicians are not provided with specific instructions on how to appraise these data. However, vital signs have been demonstrated to predict patient deterioration and we therefore hypothesize that the availability of these continuous vital sign measurements will help clinical decision-making with regard to patient discharge. There are no restrictions regarding concomitant care during the trial.

**Fig. 2 Fig2:**
[figure not shown]
Upper graph: Sensor Early Warning Score based on heart rate (HR) and respiratory rate (RR). Center and lower graphs: HR (green) and RR (orange) of a patient, respectively

After admission to the AAW, patients are either discharged home, to a nursing home, or admitted to an in-hospital ward. In all cases, for patients in the sensor group, the wearable sensor remains attached for a total of 14 days. However, after AAW stay, these measurements are no longer presented to healthcare professionals, but only analyzed retrospectively. After 14 days, the wearable sensor is removed by the patient and patients of both the control and sensor group are asked to fill in the patient questionnaire. Patient follow-up will be completed 30 days after hospital discharge.

A schedule of enrolment, interventions, and assessments of this trial is shown in SPIRIT format in Table 2 [18]. Hospital readmissions, ED revisits, and mortality are monitored until 30 days after hospital discharge. At the end of the trial, healthcare professionals are asked to fill in a questionnaire to assess satisfaction and the usability of the wearable sensor. Facilitators and barriers for implementing continuous monitoring in usual care in the AAW and at home will be assessed by patient questionnaires, healthcare professional questionnaires, and interviews with healthcare professionals.

